### 2.1. Study Design

The pilot study will follow a parallel group cluster randomized controlled trial. Randomization will be carried out at the cluster level to minimize the risk of contamination, and clusters will be defined as distinct units within LTCF residencies (i.e., separate floors or buildings, not sharing common areas or group activities, with minimal social interactions between clusters). A 6-month multicomponent intervention will be delivered and compared with usual care. Participants assigned to the multicomponent intervention will receive a 6-month program including Mediterranean diet and functional foods, physical exercise, and cognitive stimulation (see Multidomain intervention section). Participants in the intervention group will also be offered vaccinations according to the national vaccination calendar. The study protocol will include baseline evaluations (T0), a 6-month multidomain intervention, and follow-up assessments at 3 months (T1), 6 months (T2), and 9 months (T3). Participants in the control group will continue the standard care provided in their respective LTCFs, including their usual physical and cognitive stimulation activities, as well as their usual diet. Participants assigned to the control group will receive general information on healthy lifestyle and health, including risk factors. Figure 1 shows the flow diagram of the I-COUNT study protocol.

This protocol was designed in accordance with the CONSORT guidelines for feasibility and pilot studies. See the online Supplementary Materials for the CONSORT checklist figure. Participants or the public were not involved in the design of the study protocol.

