#### 2.4.1. Nutritional Intervention

The nutritional history of the participants will be evaluated at the beginning and at the end of the intervention, and then during follow-up, by collecting food habit data with a food frequency questionnaire.

Participants in the intervention group will be encouraged to follow a Mediterranean diet, in particular to consistently use extra virgin olive oil as the main fat source and to have a regular intake of nuts, and they will also consume functional foods, in particular sourdough-containing bread fortified with a vegetable matrix rich in polyphenols (e.g., olive leaves) and one probiotic vegetable (e.g., artichokes). Before starting the treatments, the functional foods will be evaluated for their functional properties (bioactive compounds, probiotics) [45]. Sourdough biotechnology has been demonstrated to improve digestibility and promote healthy microbiota metabolism at the colon level [46,47]. Moreover, olive leaves are considered a cheap source of polyphenols such as secoiridoids, flavonoids, phenylpropanoids, caffeic acid, tyrosol, and hydroxytyrosol [48]. The other approach will consider the use of a vegetable matrix enriched with Lacticaseibacillus paracasei IMPC2.1 probiotic strain, produced according to the innovative and patented procedures reported by Lavermicocca et al. [49,50], and authorized by the Italian Ministry of Health. Human feeding studies demonstrated that this probiotic strain is able to reach the gut in adequate amounts when delivered through vegetable matrices such as artichokes and table olives [51,52,53]. The final products will be characterized for their polyphenol content, and in vitro gastrointestinal digestion, using static and/or dynamic systems, will be employed to assess their potential health benefits. All the activities will be carried out with the companies in charge of developing the functional foods envisioned in this proposal.

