### 2.5. Follow-Up Assessments

Three months after the beginning of the multidomain intervention (T1), a stool sample will be collected for the analysis of the gut microbiota; this is the only assessment planned at T1. At the end of the intervention (6 months, T2) and three months later (9 months, T3), the assessments will be repeated. Furthermore, anthropometric data and blood and stool samples will be collected, together with assessments of physical and cognitive performance, at both T2 and T3. While the 6-month time point will allow us to evaluate the immediate effects of the intervention, the 9-month follow-up is intended to assess the durability of any observed effects, to evaluate whether possible improvements are maintained, attenuated or lost once the intervention is discontinued.

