### 2.7. Analytical Approach

#### 2.7.1. Outcomes

The feasibility of the multidomain intervention will be assessed by considering the acceptability and the participants’ adherence to the interventions. In particular, feasibility outcomes will include the following:Recruitment and retention rates over the study period;Adherence metrics (attendance at training sessions, completion of cognitive modules, dietary compliance);Technological acceptability, assessed via user feedback and actual usage data (wearable sensors, digital apps);Completeness and quality of data collected across domains;Operational challenges, including staffing, logistics, and data management within LTCFs.

The primary health outcome of this short-term pilot study is the evaluation of changes in gut microbiota composition and the differences between the two groups (multidomain intervention and control groups) at the 3-month follow-up point (T1). The gut microbiota has emerged as a central player in the gut–brain–muscle axis, and growing evidence suggests it may influence metabolism, inflammation, muscle function, and neurocognitive processes, making it a valuable biomarker in multidomain interventions for older adults [54].

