#### 2.7.3. Statistical Analyses

Descriptive statistics will be calculated in relation to feasibility measures (recruitment and retention rates over the study period, adherence metrics, technological acceptability, completeness of data collected and operational challenges).

Continuous variables will be compared between groups through mixed models, with random effects at the cluster level and treatment group as fixed effects. The potential health impact of multidomain interventions will be estimated considering changes over time for continuous variables analyzed through mixed models for repeated measures, with group and time, and group x time interaction as fixed effects, and cluster and patients as random effects.

The continuous variables considered in comparison between groups for fecal microbiota analyses will include measures of species richness (α-diversity), the relative abundance of specific bacterial taxa, and the representation of genes involved in key bacterial metabolic pathways. The effects of the intervention on the overall fecal microbiome composition will also be assessed comparing intervention and control groups on different time points with Bray–Curtis dissimilarity on principal coordinate analysis.

Data available for participants with complete data will be considered, but also an intention-to-treat (ITT) approach with imputation for missing data will be applied.

Results with a *p*-value < 0.05 will be considered statistically significant. Analyses will be performed using SAS software version 9.4 (SAS Institute, Cary, NC, USA).

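### The month-3 stool comparison does not separate the probiotic species fed to one arm from the residents' own microbiota, so add a strain-excluded analysis beside it

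*Protocol article*

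**What the plan says.** - **Outcome.** Section 2.7.1: "The primary health outcome of this short-term pilot study is the evaluation of changes in gut microbiota composition", compared between the arms at T1. The same measure at T2 and T3 is secondary.
- **Timing.** Section 2.1: "A 6-month multicomponent intervention will be delivered and compared with usual care". Section 2.5: "Three months after the beginning of the multidomain intervention (T1), a stool sample will be collected for the analysis of the gut microbiota". T1 is therefore halfway through feeding, T2 is at its end, and T3 is three months after it.
- **Exposure.** Section 2.4.1 includes a probiotic vegetable among the intervention arm's functional foods and names the organism: "The other approach will consider the use of a vegetable matrix enriched with Lacticaseibacillus paracasei IMPC2.1 probiotic strain". It adds that "this probiotic strain is able to reach the gut in adequate amounts when delivered through vegetable matrices such as artichokes and table olives". Dose and frequency are not given. Under section 2.1, controls keep their usual activities "as well as their usual diet".
- **Assay and analysis.** Section 2.3.4 plans metagenomic profiling of stool. Section 2.7.3 lists richness, "the relative abundance of specific bacterial taxa, and the representation of genes involved in key bacterial metabolic pathways", and Bray–Curtis dissimilarity for the community as a whole. The taxa are not named, and nothing is said about how the fed organism is handled.
- **Use of the result.** Section 2.2.1 ties the sample size to this endpoint, and the Discussion says the pilot's effect sizes will feed the sample size of a later trial.

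**The concern.** An organism supplied to one arm is measured inside the outcome on which the arms are compared. Metagenomic profiling reads the eaten strain's DNA along with everything else in the stool. The arms could then differ on the fed taxon, and possibly on Bray–Curtis composition, with no resident species changed.

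Section 2.7.1 justifies the outcome by the microbiota's place in the gut–brain–muscle axis. A reader will naturally take a positive result as a change in the resident's own gut community, and passage of an eaten strain does not show that. At stake are the wording of the microbiota conclusion, the effect size carried into the later trial, and the reading of any decline from T2 to T3, part of which could be the strain washing out.

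**Working it through.** **1. The plan's own figure.** Inputs from section 2.2.1: 60 per arm, 80% power, alpha 0.05, two-sample t-test. Normal approximation: d = (1.960 + 0.842) × √(2/60) = 2.802 × 0.1826 = 0.51. The exact two-sided t-test gives 0.516, with power 80.6% at d = 0.52. The stated 0.52 reproduces. It serves below only as a yardstick.

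**2. Exposure.** Feeding runs from month 0 to month 6, and samples fall at months 0, 3, 6 and 9. Only T0 and T3 are off product. T1, the primary one, has no washout before it.

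**3. The fed taxon.** The documents give no detection rates, so these are assumptions. Residents are treated as independent, 60 per arm. For a yes/no detection variable, SMD = (p₁ − p₀) / √{[p₁(1 − p₁) + p₀(1 − p₀)]/2}.
- 30% v 5%: 0.25 / √[(0.21 + 0.0475)/2] = 0.25 / 0.359 = 0.70 SD, power 96%. This exceeds the plan's 0.52.
- 50% v 5%: 1.17 SD, power about 100%.
- 20% v 10%: 0.28 SD, power 33% (about 25% by Fisher's exact test).

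Clustering matters. Section 2.2.2 randomises two units in each of two facilities, so there are two clusters per arm. With 30 residents per cluster, no between-cluster variance, and a cluster-level t-test on 2 df standing in for the mixed model:

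| Assumed detection, fed v control | Residents independent (Fisher) | Cluster-level test |
|---|---|---|
| 20% v 10% | about 25% | about 15% |
| 40% v 10% | about 96% | about 59% |
| 70% v 10% | about 100% | about 96% |

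**4. Bray–Curtis.** Let the resident profile be p and the strain's read share s. The fed profile is (1 − s)p plus s on the strain, so its distance from p is ½(s + s) = s. The shift equals the read share, and whether it is detected depends on the spread between residents. Two illustrative models were used, each with 150 species, 60 per arm, identical resident communities in both arms, a permutation test and 200 runs per level (Monte Carlo standard error at most 3.5 points). Model A has a mean distance of about 0.55. Model B has 90% carriage and mean distances of 0.40 to 0.59.

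| Assumed read share | A: significant | B: significant |
|---|---|---|
| 0 | 4.5% | 4% |
| 0.1% | not run | 6% |
| 0.5% | 14.5% | 31.5% |
| 1% | 34% | 82% |
| 2% | 88.5% | 100% |
| 5% | 100% | 100% |

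The share is an arm mean in A but a carrier median in B. B's arm mean is 0.9 × exp(0.8²/2) = 1.24 times the tabulated value, which explains part of the gap.

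**5. Richness.** One extra species at 90% carriage shifts the mean by 0.9. For an assumed SD of 10 to 60 species that is 0.09 to 0.015 SD, with power of 8% to 5%, essentially the null rate.

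**6. Pathway genes.** Not modelled.

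**7. Effect of removing the strain.** Dropping its reads and renormalising gives (1 − s)p / (1 − s) = p. In these models the arms are then identical, and rejection returns to about 5%.

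**The case against.** Four points have weight.

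- **The gap is read from silence.** Section 2.7.3 does not say that the strain is kept in. A fuller plan, not shown, may filter it. This stands as a limit on certainty. But the article does state its microbiota measures, including whole-community composition, and following them as written includes the strain.
- **The probiotic is part of the intervention.** Section 2.7.1 does not restrict the outcome to the resident community, so the strain's arrival belongs to the total effect of assignment. This stands. A reader might infer that the planned comparison is invalid, or that a filtered analysis must replace it. The documents support neither: which of the two is primary is a choice of question. What the unfiltered result cannot do alone is show that the resident community changed.
- **The T3 reading is largely intended.** A reader might infer that the durability answer is biased. Section 2.5 asks what remains once the programme stops, and loss of the strain is one true answer to that. It needs separate interpretation.
- **The sizes are fragile.** Detection rates and read shares are assumed. The two Bray–Curtis models disagree at 1% (34% and 82%). Section 2.7.3 names no permutation test, and it plans cluster random effects that the Bray–Curtis figures ignore. The tables show the mechanism and do not forecast this trial's rejection rate.

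The study is also a feasibility pilot that disclaims a definitive test of efficacy. That lowers the stakes, but its effect sizes are still meant for planning.

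**Conclusion.** The concern holds in limited form. T1 and T2 are on-product samples in one arm only, and the stated analysis does not distinguish the fed organism from the resident community. A difference in the fed taxon could be product carriage alone: 0.70 SD at an assumed 30% v 5% detection, but only 0.28 SD at 20% v 10%. A Bray–Curtis difference could be carriage alone if the strain holds roughly 0.5–1% of reads or more; at 0.1% the effect is negligible. These figures assume no change in resident species and, apart from the cluster-level column, independent residents. Richness is practically untouched, and the effect on pathway genes is unknown. Part of any T2–T3 decline could be washout.

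This is an inexpensive improvement that changes what the trial may conclude. It does not show that the primary comparison is wrong.

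**What to change.** In section 2.7.3:
1. Keep the unfiltered comparison and label it the total effect of assignment.
2. Prespecify beside it, for T0 to T3 and both arms, the same taxon and Bray–Curtis analyses with reads assigned to L. paracasei removed and abundances renormalised.
3. State that a change in the resident microbiota will be claimed, and effect sizes for it carried into the later trial's planning, only if it holds in the strain-excluded analysis.
4. Report L. paracasei abundance separately, as an objective marker of functional-food intake at T1 and T2 and of persistence at T3. This also serves the dietary-compliance measure in section 2.7.1 and helps interpret any T2–T3 decline.

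Cost: one filtering step on data already generated and a few lines of text, settled before the microbiota data are analysed. It needs no extra samples, visits or participants and no change to the intervention. The small downside is that species-level filtering also removes native L. paracasei, including any genuine change in it; the unfiltered analysis still shows that.

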## 3. Discussion

Aging is characterized by an increasing vulnerability to various chronic conditions, making it the primary risk factor for multimorbidity. The gradual accumulation of deficits, which notably intensifies with advancing age, is a key indicator of declining resilience and widespread imbalance across multiple bodily systems [55]. Moreover, some age-related diseases (such as dementia) have a multifactorial etiology [56]. A multimodal approach that addresses multiple risk factors and mechanisms simultaneously may be necessary to achieve optimal preventive effects.

The present pilot and feasibility study aims to evaluate the implementation of multidomain, person-based interventions for mitigating the adverse consequences of aging and improving the cognitive and functional well-being of older individuals. We propose the I-COUNT pilot protocol, which integrates physical and cognitive training, and adherence to the Mediterranean diet and to appropriate vaccinations, as a novel multicomponent intervention for older people living in LTCF settings. The I-COUNT pilot study aims to assess the feasibility of the defined protocol and to provide information to determine the sample size for a definitive study. Furthermore, this study will also provide preliminary data on cognitive, functional, and biological outcomes.

Although there is encouraging evidence regarding the effectiveness of individual programs (e.g., diet, physical exercise, or cognitive stimulation), guidelines to standardize and regulate these types of interventions are still lacking, especially in out-of-hospital care settings, where the specific equipment differs from those available for hospitalized patients. Furthermore, multidomain interventions have recently been shown to be more effective than single-domain interventions in improving frailty status, muscle mass and strength, and overall physical functioning [57]. This makes the I-COUNT project particularly valuable, as it combines interventions known to prevent disability and to improve general health and quality of life, offering a specific protocol for implementation within LTCF residences in Italy.

The domains addressed in the I-COUNT pilot protocol are crucial for preserving current abilities or delaying the onset of decline in older adults. Moreover, interventions targeting one domain often have positive effects on different domains as well. For example, the reduction in frailty score and improvements in cognitive status are significantly mediated by the composition and functionality of the gut microbiota in individuals following the Mediterranean diet [54]. The beneficial effects of physical exercise on cognitive status are also well documented [58,59]. Finally, vaccination, together with other interventions (e.g., diet, physical training) can contribute to healthy aging, also preserving the independence of older adults [60]. In our opinion, multidomain interventions represent the best option to preserve the health of older adults and protect them from frailty. We expect that positive changes might be observed in each domain during the intervention, as well as improvement in perceived quality of life and psychological status.

All the measures collected before the training and during the follow-ups (including biomarkers, physical performance, neuropsychological and psychological data) will enable us to assess the feasibility of the multidomain intervention protocol, analyze its effectiveness in detail, and to create a biobank for future studies on risk profiles related to the development of cognitive and functional disability. As a pilot and feasibility study, I-COUNT is not designed to test efficacy or effectiveness in a definitive sense but to explore whether the intervention can be successfully delivered in LTCF settings, and to identify operational, technological, and procedural aspects that may require refinement. These outcomes will provide critical information to refine intervention components, improve training procedures, and optimize data collection protocols. Importantly, data from this pilot will be used to calculate effect sizes and variability estimates, which are essential for accurate sample size calculation in a future multicenter randomized controlled trial. Moreover, qualitative and process evaluations will help us better understand barriers and facilitators to implementation in real-world aged care settings.

The present study has some limitations: first, only the feasibility of interventions is assessed, but future research should also evaluate the actual costs and benefits in the real world; second, the interventions adopted in the I-COUNT protocol (RECODE, technological instruments, etc.) need to be validated.

## 4. Conclusions

Overall, the I-COUNT pilot protocol offers a personalized and comprehensive program for older adults living in LCTF residences. If the feasibility and acceptability of the multidomain intervention are proven in this pilot study, the exploratory findings will support the design of a larger-scale trial study. The findings of this study will be potentially relevant for clinicians, healthcare providers, and caregivers, and could guide policymakers and stakeholders in recognizing the urgent need for innovative interventions in caring for older adults. This research provides a foundation for further studies in clinical practice and health policies, with the goal of building a more sustainable and effective healthcare system for aging populations.

## Figures and Tables

**Figure 1 healthcare-13-01999-f001:**
[figure not shown]
Flow diagram of the I-COUNT study. Graphical representation of the various phases of the project: recruitment, group assignment, multidomain intervention, and follow-ups.

## Data Availability

No new data were created or analyzed in this study. Data sharing is not applicable to this article.

## Abbreviations

The following abbreviations are used in this manuscript:

ACE-R	Addenbrooke’s Cognitive Examination Revised
ADL	Activities of Daily Living
ASMM	Appendicular Skeletal Muscle Mass
ASMMI	Appendicular Skeletal Muscle Mass Index
BIA	Bioelectrical Impedance Analysis
BMI	Body Mass Index
CIRS	Cumulative Illness Rating Scale
CRIq	Cognitive Reserve Index questionnaire
DASS	Depression Anxiety Stress Scale
ESS	Exton–Smith Scale
GDS	Geriatric Depression Scale
IADL	Instrumental Activities of Daily Living
I-COUNT	Multidomain Interventions to improve the COgnitive and fUNctional well-being of elderly individuals in residential sTructures
ITT	Intention-to-treat
LTCFs	Long-Term Care Facilities
MMSE	Mini-Mental State Examination
MNA-SF	Mini Nutritional Assessment-Short Form
MPI	Multidimensional Prognostic Index
MUAC	Mid-upper arm circumference
PNRR	National Recovery and Resilience Plan
PSQI	Pittsburgh Sleep Quality Index
PSS	Perceived Stress Scale
RECODE	Remote stimulation for Cognitive DEcline
SPMSQ	Short Portable Mental Status Questionnaire
SPPB	Short Physical Performance Battery
WHOQOL-BRIEF	World Health Organization Quality of Life scale
